Moreover, programs for helping with smoking withdrawal offered to young people were developed on the basis of programs for adults and do not sufficiently take into account the specific forms of tobacco addiction among the young and their needs [10]. The traditional model for adults of the progressive development of nicotine addiction (from the experimental stage to the casual stage, then daily consumption increasing in frequency until the stage of addiction) [11], does not seem to fit young smokers. Some adolescents may have experienced their first symptoms of dependence before smoking daily or began smoking daily upon experiencing their first symptoms [6]. Their smoking habit is also more influenced by their environment (family, friends, and media) [12].

Many criteria for successful smoking cessation programs for teenagers have been described in the scientific literature [8,9,13,14]. The first lecture delivered in the programs should be informative but not preachy. Accessibility of treatment programs, notably by implementing them within schools (integrating the programs during school hours), and their cost-free character (for consultation and nicotine replacement substances) are important for attracting teenagers to become involved in smoking cessation programs. Few teenagers spontaneously consult a physician for withdrawal assistance because they tend to underestimate the difficulty of quitting. The anonymity of a program as regards parents is also crucial in increasing the motivation of young people to participate. Inclusion in a program must be voluntary. Finally, programs to aid in breaking the tobacco habit should be based more specifically on the psycho-social skills of the individual and should take into account the psychological aspects involved in the process of smoking withdrawal by means of individual and collective coaching. The combination of all these factors would allow for maximizing the participation rate of teenage smokers in a program to aid smoking withdrawal.

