## Methods

This was a quasi-experimental, prospective, evaluative, comparative study. It compared 2 groups: the "intervention" group benefited from the TABADO program while the "control" group, drawn from the same training curriculum but from different VTCs, did not benefit from any specific intervention other than treatments and education that are usually available. The main objective of this study was to evaluate the efficacy a smoking withdrawal program offered as part of a comprehensive approach to prevention to all smokers in a population of young students in VTCs.

The primary outcome is the rate of smoking abstinence after 12 months, measured on the basis of the statements of the whole sample, not only among volunteers. The rate of abstinence is defined by the number of smokers who quit smoking at D_0_+12 months relative to the total number of smokers at D_0_, where D_0 _is the day of programme inception. Abstinence is defined here as quitting smoking for at least 1 month.

The secondary outcomes are three: (i) overall prevalence of tobacco usage in the study institutions at 12 months; (ii) students' motivation to quit smoking (motivational score) and frequency of attempts to quit within the 12 months after the intervention; (iii) and rate of withdrawal from the program among the volunteers after 12 months. This article deals only with the primary outcome of the study.

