### Setting and participants

This observational study will cover all students entering a participating VTC in the Lorraine region (eastern France, 2.3 million inhabitants, 51 centers, 16,500 vocational trainees), during the school years 2007-2008 and 2008-2009. Students from vocational training courses with at least 2 years duration will be eligible. The control group will consist of students in the same kinds of courses, in different VTCs. Thus, the control group will have a psycho-socio-economic-cultural profile similar to that of the experimental group, without the control subjects being involved by the participants in smoking cessation, which might have occurred if the control subjects had belonged to the same VTC [16].

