#### Monitoring data for all students

An initial assessment questionnaire on the smoking status of each trainee, socio-demographic data, knowledge, attitude, and behaviour will be completed by all students during the first visit, which will take place in the same period for both groups. A final questionnaire to evaluate smoking status will be completed at D_0_+12 months. It will contain the items included in the initial questionnaire and items allowing for assessment of changes in the perception of the health risks of smoking among trainees. The questionnaire will also include questions to measure changes over time in tobacco consumption among smokers. Thus, it will allow an overall assessment of the effectiveness of the intervention among the target population.

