### Data analysis

The experimental and control groups will be compared for abstinence rates reported at 12 months after the intervention by use of multivariate logistic regression adjusting for predefined characteristics (age, sex, and training course). The analysis will be "in intention to treat". All the smokers from the institutions will be taken into account, and subjects lost to follow-up will be considered non-abstaining smokers.

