The group nature of the intervention and the risk of "behavioural contamination" require cluster sampling, rather than individual sampling. Given the small number of institutions and their great heterogeneity in terms of training programs, we preferred a reasoned attribution rather than randomization, which might not yield comparable groups and would not be effective in this case [16]. Our intervention is a community-based intervention (i.e. interventions in which the unit of allocation to receive preventive regimen is an entire community [25]. In other words, judgment criteria are measured over the entire population rather than among volunteers only. The main risk is a dilution of the effect in the case of low participation [26].

Finally, we chose the rate of continuous abstinence after 1 year to ensure optimal conditions for evaluation: the period of 1 year is usually accepted as a general long-term monitoring standard [27].

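### Centres were allocated by judgement, but the primary model adjusts only for age, sex and training course, so confounding by baseline consumption, motivation and social background may remain

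*Protocol article*

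**What the plan says.** Methods introduces the design thus: "This was a quasi-experimental, prospective, evaluative, comparative study". To explain why it did not randomise, the Discussion points to how few the centres are and how much their training programs differ. It then says: "we preferred a reasoned attribution rather than randomization, which might not yield comparable groups". The comparability doubt in that sentence is about randomisation; the authors expected deliberate allocation to do better.

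Setting and participants takes controls from the same kinds of courses in other VTCs and concludes: "Thus, the control group will have a psycho-socio-economic-cultural profile similar to that of the experimental group". The article describes no check of this.

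Data analysis specifies multivariate logistic regression on all baseline smokers, counting those lost to follow-up as still smoking, "adjusting for predefined characteristics (age, sex, and training course". The list is closed, and no other control of confounding is mentioned.

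On baseline data, Monitoring data for all students states: "An initial assessment questionnaire on the smoking status of each trainee, socio-demographic data, knowledge, attitude, and behaviour will be completed by all students". This takes place in the same period in both groups. The following section reserves the in-depth assessment of consumption for smokers who volunteer for the program.

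**The concern.** In a non-randomised comparison, the effect estimate depends on how well the design and the model together make the groups comparable. Here the design matches on type of course and the model adjusts for course, age and sex. Two centres teaching the same trade can still differ in how much their smokers smoke, how ready they are to quit, and the homes and friends they come from.

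The article itself treats such factors as relevant. Background says of adolescents: "Their smoking habit is also more influenced by their environment (family, friends, and media". Methods makes motivation to quit a secondary outcome. Yet the primary model uses none of the baseline smoking, attitude or behaviour data gathered from every trainee, and no socio-demographic item beyond age, sex and course. If the groups differ on these factors, the difference goes into the estimated program effect. It could create an apparent benefit or hide a real one.

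**Working it through.** **1. The plan's own figure.** Inputs from Sample size calculation: 5% against 10% abstinence, two-sided α of 5%, power 85%, equal groups. The 10% is 0.5 × 15% + 0.5 × 5%. With pooled variance and no continuity correction:

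n = [1.960 × √(2 × 0.075 × 0.925) + 1.036 × √(0.05 × 0.95 + 0.10 × 0.90)]² / 0.05² = (0.730 + 0.384)² / 0.0025 ≈ 497 per group.

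The stated 500 is reproduced, and power at 500 is 85.2%. This calculation assumes comparable groups and makes no allowance for confounding. Expected abstainers: 500 × 0.05 + 500 × 0.10 = 25 + 50 = 75.

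**2. Size of possible confounding.** The article gives no baseline imbalance and no covariate effect, so the inputs below are assumptions:

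- no true program effect; control abstinence 5%; 500 smokers per group;
- one binary baseline factor that favours quitting (for example, light consumption or high motivation), present in 30% of controls;
- odds ratio of the factor for quitting: 2, 3 or 4;
- the factor is 10, 20 or 30 percentage points more common in the intervention group, read as the imbalance left after adjustment for age, sex and course.

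Let b be abstinence without the factor and a abstinence with it, so that a/(1−a) = OR × b/(1−b) and 0.3a + 0.7b = 0.05. With imbalance d, intervention abstinence is p₂ = (0.3 + d)a + (0.7 − d)b, and the spurious difference is p₂ − 0.05 = d(a − b).

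Middle case (OR 3, d = 0.20): b = 0.0324 and a = 0.0912.
- p₂ = 0.5 × 0.0912 + 0.5 × 0.0324 = 0.0618, a spurious +1.2 points.
- Spurious odds ratio: (0.0618/0.9382) / (0.05/0.95) = 1.25.
- Standard error: √(0.05 × 0.95/500 + 0.0618 × 0.9382/500) = 0.0145, so z = 0.0118/0.0145 ≈ 0.81.
- Chance of a significant result: Φ(0.81 − 1.96) + Φ(−0.81 − 1.96) ≈ 13%.

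| Factor OR | Imbalance (points) | Spurious difference (points) | Spurious OR | Chance of p < 0.05 |
|---|---|---|---|---|
| 2 | 10 | 0.36 | 1.08 | 5.8% |
| 2 | 20 | 0.72 | 1.15 | 8.0% |
| 2 | 30 | 1.09 | 1.23 | 11.7% |
| 3 | 10 | 0.59 | 1.12 | 7.0% |
| 3 | 20 | 1.18 | 1.25 | 12.8% |
| 3 | 30 | 1.76 | 1.38 | 22.0% |
| 4 | 10 | 0.74 | 1.16 | 8.2% |
| 4 | 20 | 1.49 | 1.32 | 17.3% |
| 4 | 30 | 2.23 | 1.48 | 31.4% |

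The spurious difference is proportional to d, so an imbalance in the opposite direction gives the same size with a negative sign. The probabilities treat smokers as independent; clustering by VTC is a separate matter.

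**3. Which data could be used.** The analysis set is smokers at baseline, so smoker or non-smoker status cannot serve as a covariate. Useful items would be amount smoked, motivation or attitude to quitting, and a socio-economic item. The all-student questionnaire covers these domains in general terms, but the article does not list its questions. The in-depth assessment does not exist for controls.

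**The case against.** Much can be said for the plan, and several stronger readings should be set aside.

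- *That the article contradicts itself on comparability.* A reader might set the heterogeneity of centres in the Discussion against the similarity claimed in Setting and participants. But the heterogeneity is stated in terms of training programs, which same-course selection and adjustment for course address. Nothing is said about heterogeneity in smoking or motivation.
- *That covariate adjustment is the only protection.* It is not. Both groups come from one region, the same kinds of courses, the same age range and the same minimum course length, with baseline measured in the same period. These protections are real, but none acts directly on consumption, motivation or social background.
- *That the estimate is confounded.* No baseline imbalance is reported, so the documents support only that it may be.
- *That the strongest predictors of quitting were collected from everyone and left out.* The documents do not rank predictors, and they do not show that dependence, past quit attempts or family and peer smoking were asked of all trainees. The Background sentence on environment is not a list of collected variables.
- *That the bias could be most of the planned effect.* With assumed abstinence of 20% in light smokers and 3% in daily smokers, a 20-point imbalance gives 0.20 × 0.17 = 3.4 points. But a 5% overall control rate then implies (0.05 − 0.03)/0.17 ≈ 12% light smokers among controls, against about 32% in the intervention group. Nothing in the article supports so large a gap between same-course groups.

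One could also say that an article condenses and the full plan may hold more. That would excuse a missing detail, but here the adjustment set is stated as predefined and closed, and the criticism is of that choice.

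**Conclusion.** The point holds as a possible, not a demonstrated, bias. Centres were allocated by judgement, and the stated adjustment set covers course, age and sex but not baseline consumption, motivation or attitude, or social background. Size and direction of any remaining confounding are unknown.

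Under the assumptions shown, the spurious difference is about 0.4 to 2.2 points, against a planned effect of 5, and the false-positive chance is about 6% to 31% instead of 5%. The middle case, 1.2 points and about 13%, is a fairer guide than the top of the range, which needs the factor in 60% of one group and 30% of the other. The plan should be changed because the comparison is not randomised and the change draws on a questionnaire already planned for everyone.

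**What to change.** 1. In Data analysis, extend the predefined adjustment set by a small number of items from the baseline questionnaire completed by all trainees: for example baseline consumption, motivation or attitude to quitting, and one socio-economic item, as far as each was asked of everyone in both groups. Enter them as covariates or summarise them in one score. Name them before the 12-month outcome is examined.
2. Do not use the volunteers-only in-depth assessment for this purpose.
3. In Setting and participants, reword the similarity of the groups as an assumption to be checked at baseline.

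The cost is a change of wording and a modest amount of analysis, with no new data. The downside is a few more parameters with about 75 expected abstainers, so the added terms must be few. Individual-level adjustment, including a score, does not remove differences that act at VTC level; those are a separate issue.

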### Sample size calculation

According to the literature, we can assume a maximum 5% spontaneous withdrawal rate [17]. We hope to double this rate among participants in the experimental group after 1 year. This 10% rate is based on the assumption of an effective participation of 50% of smokers in the experimental group, with a smoking cessation rate of 15% among them and the regular 5% for non-volunteers in the experimental group. With two groups of the same size, an α two-sided risk of 5% and a power of 85%, the number of smokers per group must be 500. Thus, the total number of students to be included is 2000 (anticipating that the prevalence of smoking is 50%).

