#### Monitoring data for smokers who volunteer for the program only

The in-depth assessment of tobacco consumption of volunteers will be based on a questionnaire used by the tobacco addiction specialist and on the case report form. Monitoring over time of the volunteer's tobacco consumption will be provided by 4 questionnaires completed by volunteers at each visit with the tobacco addiction specialist. At 6 months after the start of the intervention, volunteers will complete a follow-up questionnaire.

Ethical approval for the trial was requested from Inserm (*Institut National de la Santé et de la Recherche Médicale *- National Health and Medical Research Institute). The protocol was submitted to the national scientific and ethical bodies involved (CCTIRS and CNIL), who gave their approval. Written consent from the subjects participating in the program was collected by one of us (LM), after subjects were given information about the program and the study, as well as their right to refuse to take part in the program or to leave it at any time. Two types of data and consent forms were used: one aimed at volunteer aged less than 18 and their legal representatives (parents or guardian) and the other addressed to adult volunteers [>18 years].

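### The sample size has no term for loss to follow-up, although the primary analysis counts every loss as a smoker, so equal loss brings power below the stated 85%

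*Protocol article*

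**What the plan says.** All places are in the Methods of the protocol article.

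- **Sample size calculation.** For the control rate, "we can assume a maximum 5% spontaneous withdrawal rate". For the intervention group, "We hope to double this rate among participants in the experimental group after 1 year". The 10% is a mixture: it assumes "an effective participation of 50% of smokers in the experimental group". Those who take part are given a quit rate of 15%, and the remaining intervention smokers keep the 5%. With equal groups, a two-sided 5% level and 85% power, this leads to 500 smokers per group. The step to 2000 students uses only the 50% smoking prevalence.
- **Opening of Methods.** The abstinence rate is taken over all who smoked at programme start.
- **Data analysis.** The comparison is by intention to treat, includes all smokers from the institutions, and "subjects lost to follow-up will be considered non-abstaining smokers".
- **Data collection.** All students complete a questionnaire at baseline and at 12 months. Volunteers in the programme also have "4 questionnaires completed by volunteers at each visit with the tobacco addiction specialist", and another questionnaire at 6 months.

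No expected loss rate and no inflation for loss appear anywhere in the article.

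**The concern.** Keeping lost smokers in the denominator and scoring them as failures preserves the number analysed but not the power. Any of them who did quit is no longer counted. Both observed rates fall, and the absolute difference falls with them. A power of 85% computed at 5% versus 10% therefore describes a trial with complete follow-up, or one whose planning rates were already on the losses-as-failures scale. The article claims neither. Its own missing-data rule shows that some loss is expected. If the stated power is too high, a programme that works as hoped has a larger chance of being reported as not shown effective than the plan admits.

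A second, smaller issue is the direction of the rule. Scoring losses as smokers lowers the rate more in the group that loses more people, so it is not conservative for the comparison between groups. Volunteers have study contacts that controls do not have, so unequal retention is possible.

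**Working it through.** **Inputs.** From the Sample size calculation: p₁ = 0.05, p₂ = 0.10, two-sided α = 0.05, power 0.85, n = 500 smokers per group, participation 50%. The loss proportion L is not given; 10%, 20% and 30% are assumed to show a range.

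**1. The plan's own figures.** The mixture is 0.5 × 15% + 0.5 × 5% = 10%, with no term for loss. With p̄ = (p₁ + p₂)/2, the usual two-proportion formula is

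n = [1.960 √(2p̄(1−p̄)) + 1.036 √(p₁(1−p₁) + p₂(1−p₂))]² / (p₂−p₁)²

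Here p̄ = 0.075, so n = [1.960 × 0.3725 + 1.036 × 0.3708]² / 0.05² ≈ 497. Power at 500 per group is 85.2%. The step to students is 2 × 500 / 0.50 = 2000. The stated figures are reproduced, and the rounding from 497 to 500 is the only slack. A continuity correction would need 536 per group, so it would not reveal a margin either.

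**2. Equal loss under the planned rule.** Assume that smokers lost to follow-up quit at the same rate as the others in their group. Then p₁ becomes 0.05(1−L) and p₂ becomes 0.10(1−L), while n stays at 500.

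For L = 20%, the rates are 4% and 8%, and p̄ = 0.06. The standard error under no difference is √(2 × 0.06 × 0.94 / 500) = 0.01502. Under the alternative it is √((0.04 × 0.96 + 0.08 × 0.92) / 500) = 0.01497. Then z = (0.04 − 1.960 × 0.01502) / 0.01497 = 0.706, which gives a power of 76.0%.

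| Loss in both groups (assumed) | Observed rates | Difference (points) | Power, 500 per group | Smokers per group for 85% | Students at 50% prevalence |
|---|---|---|---|---|---|
| 0% | 5.0% vs 10.0% | 5.0 | 85.2% | 497 | 1988 |
| 10% | 4.5% vs 9.0% | 4.5 | 81.0% | 557 | 2228 |
| 20% | 4.0% vs 8.0% | 4.0 | 76.0% | 632 | 2528 |
| 30% | 3.5% vs 7.0% | 3.5 | 69.9% | 728 | 2912 |

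The last column is the per-group number × 2 / 0.50. Clustering by training centre is a separate matter and is not included.

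**3. Unequal loss, as an illustration.** Suppose there is no true effect (5% in every group), and only the volunteers, 50% of intervention smokers, are better retained: 10% loss against 30% for everyone else.

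- Intervention loss: 0.5 × 10% + 0.5 × 30% = 20%. Control loss: 30%.
- Observed rates: 5% × 0.80 = 4.0% against 5% × 0.70 = 3.5%.
- Odds ratio: (0.040/0.960) / (0.035/0.965) = 1.15.
- The nominal two-sided rejection probability is about 7% instead of 5%.

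The upper limit by this route, with no volunteer lost and 30% loss elsewhere, is 15% against 30%. The rates are then 4.25% against 3.5%, and the odds ratio is 1.22.

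**The case against.** Four arguments deserve an answer.

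- **The rule is accepted practice.** Scoring losses as smokers fits the outcome's denominator of all baseline smokers. This stands: the rule is not an error and can remain primary. The mismatch lies in the sample size.
- **The 5% and 10% may already be on that scale.** The outcome definition makes this possible. If it is so, the dilution above does not apply. But the Sample size calculation does not say it, and its mixture contains cessation and participation rates only.
- **The 5% is called a maximum.** If the spontaneous rate were 4% and volunteers still reached 15%, the mixture would be 0.5 × 15% + 0.5 × 4% = 9.5%. Power for 4% versus 9.5% is about 93.5%, and about 87% at 20% loss and 82% at 30%. If the programme doubles the rate instead, 4% versus 8% gives 76% before any loss. The text supports either reading, so this is not a dependable margin.
- **A fuller protocol or analysis plan may deal with missing data in detail.** This stands for imputation models and loss tables, whose absence from an article is no finding. It does not settle the power question, because the rule and the calculation are both stated here.

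A reader might infer a larger bias, for example 30% loss in controls against 10% in the intervention group, for an odds ratio of about 1.30. The extra contacts cannot produce this. They reach only half of the intervention smokers, and with the other half lost at 30% a group loss of 10% would need a volunteer loss of −10%. A reader might also infer that the rule will favour the programme. The article documents neither the size nor the direction of any difference in loss. The programme sessions are spread over 3 months, the volunteer questionnaire is at 6 months, and the 12-month questionnaire goes to everyone.

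**Conclusion.** The point holds as a mismatch between the sample size and the primary analysis. The stated 85% uses up the planned 500 smokers per group at 5% versus 10%. Under the planned rule, equal loss of 10%, 20% or 30% gives about 81%, 76% or 70%.

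This rests on three assumptions: the planning rates are true cessation rates, lost smokers quit at the same rate as the others, and loss is equal between groups. The loss rates themselves are assumed. The overstatement is therefore conditional. If the intervention group were better retained, nominal power could rise instead, but through bias.

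The two harms belong to different scenarios and should not be added together. Equal loss costs power and creates no difference when there is no effect. Unequal loss shifts the comparison towards the better-retained group. That shift is secondary: an odds ratio of about 1.15 in the illustration, in a direction the article does not establish. Nothing here invalidates the trial or the choice of primary rule.

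**What to change.** **Main change, in the Sample size calculation.** Do one of the following:

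- State the expected 12-month loss and restate the power with 500 smokers per group at the diluted rates (for example 76% at 20% loss).
- State that the 5% and 10% already count losses as failures, and give the basis for that.

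The cost of the first is a sentence or two and a less favourable stated power; the second costs a sentence. If 85% is to be kept at the diluted rates, the cost is the larger sample in the table.

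**Secondary change, in the Data analysis section or the analysis plan.** Keep losses scored as smokers as the primary analysis. Add one sensitivity analysis that varies the abstinence rate among the missing separately in the two groups, unless the analysis plan already has it. The cost is a sentence and a small amount of analysis, with no new data.
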